### Standard Precautions

We used the same standard precautions for both training groups and modified them for each individual participant, after evaluation and recommendation by the PI. These included the following:

Decrease in exercise intensity for systolic blood pressure greater than 200 mm Hg or diastolic blood pressure greater than 100 mm Hg.Decrease in exercise intensity, if HR was greater than 75%.Pause in training on observation of dyspnea or if blood pressure dropped below resting pressure.Pause in training if participant reported symptoms of light-headedness.

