### Training Paradigms

#### Hands-Free Body Weight Support Gait Training

This group served as our “control,” in that participants did not perform any additional essential challenging mobility skills during their 6-week training period. We felt that the inclusion of an active training control group was necessary to determine if adding essential challenging mobility skills practice to a gait training program would improve walking outcomes above and beyond improvements gained from walking practice alone. However, it is important to note that because of the safety features of our robotic device, we were able to eliminate provision of handrail support and/or manual assistance from the clinician. Although walking upright with handrail support can provide sufficient training challenge and fall safety, because of poor hemiparetic trunk control stroke, survivors are likely to adopt stooped postures by leaning forward and holding onto handrails for trunk support [40]. Such postures not only decrease training intensity and metabolic output but also minimize functional improvements [41,42]. Thus, treadmill training without handrail support can offer a more practical dynamic balance challenge that pertains to real-world independent ambulation. In addition, we did not offer participants any walking instructions (eg, how to step or correct their movements) and did not offer any passive assistance during training. Our governing principle regarding walking rehabilitation post stroke was to provide the individual with a safe environment to practice walking, solve the problem, and learn from mistakes during training. We followed AHA guidelines for exercise training [16]. Participants in this group walked for a total duration of 30 min per session, at 60% to 80% of their heart rate (HR) reserve (ie, moderate to high intensity) based on the Karvonen formula [43] with or without their prescribed BWS level (ie, between 0 and 30% support; assigned as described below). By taking advantage of the KA interface’s safety mechanism and DOF, participants in this group were able to explore their limits of stability while controlling the treadmill belt speed, and thus, train independently without assistance or external support.

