### Participant Training Intensity Heart Rate Zone Determination for Each Training Session

We documented all participant’s baseline blood pressure and HR before commencement of each training session. We calculated the maximum HR for each participant using their age (ie, HR_max_=220 − age) and calculated the desired 60% to 80% training intensity using the Karvonen formula (ie, training intensity=(max HR − resting HR) × (desired %) + resting HR) based on AHA training recommendations [16]. If the participant was taking a beta-blocker, we revised this formula to use a max HR calculated as HR_max_=164 − age [44]. Thus, we individually customized the participant’s training intensity for each session. We encouraged participants to walk fast enough during training to achieve these zones; however, we also measured rating of perceived exertion (RPE; see below) to obtain a proxy measure of training intensity in the event that HRs did not reach the desired intensity. We used a GARMIN HR monitor that was strapped to each participant’s chest to record actual HR measurements for each session. We recorded HR values each minute; thus, we recorded a total of 30 HR values per training session (6 × 5-min bouts=30 min).

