Session design	5-min bouts × sets, or as long as continuously tolerated	5-min bouts × 6 sets, or 10-min bouts × 3 sets to allow for skill changes
Session goal	Target 60% to 80% of heart rate reserve during all trials	Target 60% to 80% of heart rate reserve during all trials
Locomotor challenge	Hands-free and without manual assistance	3 new randomized locomotor total challenges per day × 3 sessions=9 per week
Instruction	Maintain heart rate in the target zone while walking	Maintain heart rate in the target zone while performing different walking skills
Physiological measures monitored	Heart rate—using heart rate, monitor each minute; rate of perceived exertion—using Borg scale every 2 min; blood pressure—pre/post	Heart rate—using heart rate monitor each minute; rate of perceived exertion—using Borg scale every 2 min; blood pressure—pre/post
Additional session measurements	Total number of steps (using step watch) and distance covered (using distance wheel)	Total number of steps (using step watch) and distance covered (using distance wheel)
Rest breaks	Every 5 min if necessary; standing breaks if heart rate exceeded zone; voluntary breaks if requested by participant (rare)	Every 5 min if necessary; standing breaks if heart rate exceeded zone; voluntary breaks if requested by participant (rare)
Training personnel	Physical therapist × 1; research assistant × 1	Physical therapist × 1; research assistant × 1
Training setting	Clinical laboratory	Clinical laboratory

^a^BWS: body weight support.

^b^10MWT: 10-meter walk test.

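### The reduce-intensity trigger at 75% names no base and conflicts with the prescribed 60% to 80% of heart rate reserve on either reading

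*Protocol article*

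**What the plan says.** All references are to the Protocol article.

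- **Target.** The hands-free training section has participants walk "at 60% to 80% of their heart rate (HR) reserve (ie, moderate to high intensity) based on the Karvonen formula". The challenge-training section gives the same range of reserve, and the section on heart rate zones gives the same percentages with the formula. Table 2 sets the session goal for both groups as "Target 60% to 80% of heart rate reserve during all trials".
- **Break rule.** Table 2 allows "standing breaks if heart rate exceeded zone", so this rule acts only above 80% of reserve.
- **Precaution.** Standard Precautions says "Decrease in exercise intensity, if HR was greater than 75" percent, with no base.
- **Blood pressure.** Standard Precautions lowers intensity above 200 systolic or 100 diastolic, and pauses training "if blood pressure dropped below resting pressure". Table 2 lists "blood pressure—pre/post", next to heart rate each minute and perceived exertion every 2 minutes.
- **Beta-blockers.** The heart rate zone section states "we revised this formula to use a max HR calculated as HR_max_=164 − age", used in the same Karvonen formula. The exclusion criteria rule out a resting rate only above 100, and the inclusion criteria set no upper age limit.

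**The concern.** Two explicit numerical rules govern the same heart rate in the same session, and staff cannot follow both across the whole target zone. This bears on safety and also on the data. Similar cardiovascular intensity in the two arms is a stated premise of the design (Introduction), and Subgroup Analysis plans to assess whether participants could hold the target heart rate. If some staff eased participants off at 75% and others let them run to 80%, a low share of minutes in the upper zone may reflect the rule applied rather than the participant's ability. For a beta-blocker user whose computed zone sits at or below rest, being in the target zone has no clear meaning.

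**Working it through.** There is no stated figure to reproduce, so the check applies the document's own formulas. Ages and resting rates are illustrative values within the eligibility limits.

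**Inputs.** Target = (M − R) × p + R, with M the maximum and R the resting heart rate. M = 220 − age, or 164 − age with a beta-blocker. p runs from 0.60 to 0.80. R is at most 100 at screening.

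**1. The 75% read as percent of reserve.** The share of the band above the trigger is (80 − 75)/(80 − 60) = 25%, for every participant with M above R. At age 60, R = 70, M = 160:
- lower bound: 90 × 0.60 + 70 = 124
- trigger: 90 × 0.75 + 70 = 137.5
- upper bound: 90 × 0.80 + 70 = 142

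From 137.5 to 142, one section prescribes the intensity and another calls for lowering it.

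**2. The 75% read as percent of maximum.** The same participant has a trigger of 0.75 × 160 = 120, below the lower bound of 124. In general the trigger is below the whole zone when 0.75M < 0.60M + 0.40R, that is, R > 0.375M. At age 60 this means R above 60. With a lower resting rate the trigger falls inside the zone: at age 50, R = 60, M = 170, the zone is 126 to 148 and the trigger 127.5. It can never clear the top of the zone, because 0.80M + 0.20R always exceeds 0.75M. Neither reading removes the conflict.

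**3. Table 2 against the precaution.** Table 2 provides a break only when heart rate exceeds the zone (142 in the example). The precaution acts earlier, at 137.5 or 120. They are two different ceilings.

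**4. Blood pressure.** Every reading described (heart rate zone section, Table 2, and the two sections on session duration and time) is before or after training. The pre-session reading can set off the systolic or diastolic rule. A drop below resting pressure during training has no stated reading to reveal it.

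**5. Beta-blocker formula.** The target is R + p(M − R), so it equals R when M = R and is below R when M < R, that is, when R > 164 − age. The bounds then also reverse.

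| Age | R | M = 164 − age | 60% | 80% |
|---|---|---|---|---|
| 64 | 100 | 100 | 100.0 | 100.0 |
| 65 | 100 | 99 | 99.4 | 99.2 |
| 75 | 90 | 89 | 89.4 | 89.2 |
| 85 | 80 | 79 | 79.4 | 79.2 |
| 70 | 80 | 94 | 88.4 | 91.2 |
| 70 | 70 | 94 | 84.4 | 89.2 |

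The last two rows stay above rest but are narrow: 0.20 × (94 − 80) = 2.8 beats and 0.20 × (94 − 70) = 4.8 beats. At R = 70 the target falls below rest only above age 94. With 220 − age and R no higher than 100, it cannot fall below rest until past age 120.

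**The case against.** The strongest reply is that the precautions were defaults: Standard Precautions says they were adapted to each participant on the principal investigator's recommendation, and the principal investigator oversaw all sessions. Perceived exertion was also kept as a proxy when heart rate did not reach target. Both facts soften the practical effect. Neither says which ceiling applied, so the text remains unreconciled.

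Other parts of the reply stand and limit the point:

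- A reader might infer that none of the blood-pressure rules could operate. The documents do not support that: the pre-session reading serves the systolic and diastolic thresholds. The Table 2 entry is a summary, and the full protocol may describe further readings. Only the pause for falling pressure lacks a stated one.
- A reader might see a contradiction in admitting a resting diastolic up to 110 while easing intensity above 100. There is none. One rule governs enrolment and the other training, and both can be followed.
- A reader might take the beta-blocker formula to fail generally. It does so only for older users with a fairly high resting rate. The article gives neither the number of beta-blocker users nor the distribution of resting rates.
- A reader might conclude that the walking-speed comparison is biased. Target and precautions were the same in both arms, and nothing in the text makes the ambiguity act differently between them.

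**Conclusion.** The conflict between the 75% trigger and the 60% to 80% target is real on either natural reading. It covers a quarter of the band if the base is reserve. If the base is maximum heart rate, it covers the whole band whenever resting rate exceeds 0.375 of the maximum, and part of it otherwise. This rests only on the printed formulas and thresholds. The missing in-training blood-pressure reading is a narrow gap. The beta-blocker collapse is permitted by the eligibility rules but of unknown frequency.

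The consequence is confined to the clarity of the safety rules and the interpretation of target heart rate attainment, which is neither the primary outcome nor a listed secondary one. Heart rate was logged each minute, so delivered intensity can still be described. This is a correction worth making at low cost, not a defect that puts the primary analysis in doubt.

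**What to change.** Reconcile Standard Precautions with the two training sections, the heart rate zone section and Table 2. Name the base of the 75%, and make the target, the break rule and the precaution consistent. State which blood-pressure reading serves the pause rule. Check the beta-blocker formula against its cited source and against the resting heart rate limit in the exclusion criteria. Which threshold or formula is right is for the clinical team; none is proposed here.

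In the heart rate attainment report, state which ceiling was applied in practice, and flag beta-blocker users whose computed zone falls to or below rest, with their number.

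Training and follow-up ended by January 2016, so only the text and the reporting can change. The cost is a short clarification by the clinical team and one added descriptive breakdown from data already recorded.

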#### Challenge With Hands-Free Body Weight Support Gait Training

This group served as our “experimental” group, in that participants additionally performed 9 different essential challenging (C) mobility skills, along with HF walking during their 6-week training period (Table 1). The purpose of practicing these 9 essential training challenges along with HF walking was to offer participants opportunities to navigate through common environmental hazards that they may encounter during community ambulation. This protocol was innovative, as it involved exposing stroke survivors to challenging tasks that required strong skills in anticipatory and reactive balance and functional mobility. The KA’s safety features allowed us to provide participants with this experience and to treat losses of balance or stumbles as “learning experiences,” from which participants could learn to formulate new strategies without any negative consequences. At the start of each training week, the program coordinator would randomly select and assign 3 challenges for each session using a random number generator [27]. Participants practiced training for each of the 3 skills for 30 min (10 min per skill), without handrail support at 60% to 80% of their HR reserve intensity per session. We did not have a prescribed challenge progression for each skill; however, we encouraged participants to perform each skill at a level that was challenging for them (see task difficulty, Table 1).

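### The 75% heart-rate precaution has no stated base and conflicts with the target zone of 60–80% of heart rate reserve, so the permitted upper limit is unclear

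*Protocol article*

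**What the plan says.** **Target.** In the protocol article, Hands-Free Body Weight Support Gait Training has participants walk "at 60% to 80% of their heart rate (HR) reserve". The section on the challenge arm sets the same band: "without handrail support at 60% to 80% of their HR reserve intensity per session". Table 2 gives one session goal for both arms: "Target 60% to 80% of heart rate reserve during all trials". The section on determining the HR zone says the investigators "calculated the desired 60% to 80% training intensity using the Karvonen formula", with maximum HR taken as 220 − age, or 164 − age on a beta-blocker. It adds: "We encouraged participants to walk fast enough during training to achieve these zones".

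**Action above the zone.** The rest-break row of Table 2, identical in both arms, includes "standing breaks if heart rate exceeded zone". The same cell also allows breaks every 5 minutes if needed and on request.

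**Precaution.** Standard Precautions lists "Decrease in exercise intensity, if HR was greater than 75" per cent. The base of the percentage is not named. The precautions are the same for both groups, but the investigators "modified them for each individual participant, after evaluation and recommendation by the PI".

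**Use of the data.** HR is logged every minute and perceived exertion every 2 minutes. Subgroup Analysis plans to assess how well each group maintained the target HR intensity.

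**The concern.** A participant at, say, 78% of reserve is on target by Table 2, yet may already have passed the point at which Standard Precautions calls for less effort. The text does not say which instruction prevails, and the missing base decides whether the overlap is small or covers most of the zone.

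Two things depend on this. First, it is a safety threshold, and a reader cannot apply a percentage without its base. Second, ability to hold the target HR is a planned result, and the Discussion says the study will show whether people after stroke can train at higher intensities. The HR log shows what rate was reached. It does not show whether a lower rate reflects the participant's capacity or staff easing the effort under the precaution.

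**Working it through.** The article states no figure to reproduce here, so the check applies its own formula to both readings of the 75%.

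**Inputs from the article**
- Karvonen formula: HR at fraction p = (M − R) × p + R, where M is maximum HR and R is resting HR.
- M = 220 − age, or 164 − age on a beta-blocker.
- Zone: p = 0.60 to 0.80.
- Resting HR above 100 bpm is excluded at entry.

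**Assumptions.** The article gives no participant ages or resting rates. The worked example takes age 60, R = 70 and no beta-blocker. The grid takes ages 40, 50, 60, 70 and 80 with R = 50, 60, 70, 80, 90 and 100.

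**Reading A: 75% of reserve**
- Share of the zone above the precaution: (80 − 75) / (80 − 60) = 5/20 = 25%, whatever the age or resting rate.
- Example: M = 160 and reserve = 160 − 70 = 90.
  - Floor: 0.60 × 90 + 70 = 124 bpm.
  - Ceiling: 0.80 × 90 + 70 = 142 bpm.
  - Precaution: 0.75 × 90 + 70 = 137.5 bpm.
  - Conflict: 142 − 137.5 = 4.5 bpm of an 18 bpm zone.
- From 60% to 75% of reserve both rules are met.

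**Reading B: 75% of maximum HR**
- Example: 0.75 × 160 = 120 bpm, which is 4 bpm below the 124 bpm floor. The whole zone would call for a reduction.
- General condition: the threshold is below the floor when 0.75M < 0.60M + 0.40R, that is, when R > 0.375M.
- Without a beta-blocker this means R above 67.5 bpm at age 40 (M = 180), above 60 bpm at age 60 (M = 160) and above 52.5 bpm at age 80 (M = 140).

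| Grid | Pairs | Threshold below floor | Threshold at floor or inside zone |
|---|---|---|---|
| No beta-blocker | 30 | 22 | 8 |
| Beta-blocker (pairs with M > R) | 27 | 27 | 0 |

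One of the 8 pairs (age 60, R = 60) sits exactly on the floor, at 120 bpm.

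**Comparison.** 75% of maximum HR is always less than 75% of reserve HR, because 0.75M < 0.75M + 0.25R for any R > 0. Reading A is therefore the smaller conflict, and some conflict exists on either reading.

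**The case against.** The strongest reply is that every HR percentage with a stated base in the article is of reserve. Maximum HR appears only as an input to the Karvonen formula. On a beta-blocker, the maximum-HR reading can even put the threshold below resting HR: at assumed age 60 and R = 80, 0.75 × 104 = 78 bpm. On the reserve reading, someone eased back from 76% stays in the zone. The precaution asks for less effort, not a stop, and Table 2 prescribes a different action above the zone, so the two could be steps of one graded response. The target and the listed precautions are the same in both arms. Case-by-case modification by the principal investigator also allows flexibility.

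Much of this stands, and it rules out several stronger readings that a reader might infer:
- **Obeying one rule breaks the other.** On the reserve base this is true only between 75% and 80%. Obeying the precaution does not take anyone out of the zone, and so would not by itself explain failure to reach 60%.
- **The whole zone is ruled out.** This needs the maximum-HR reading together with assumed ages and resting rates.
- **Delivered intensity is undefined.** It is measured, by HR each minute and perceived exertion every 2 minutes.
- **The arms were limited differently.** Individual modification makes this conceivable, but nothing in the article shows it.

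The reply does not remove the contradiction. The article nowhere describes a graded response, does not name the base, and sets a target running to 80% beside an instruction to reduce effort above 75%. Individual modification changes the limits person by person without saying what the default was.

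**Conclusion.** The point holds in a narrow form. The article gives two upper HR limits that cannot both apply as written, and one of them lacks a base. On the reserve base the conflict is 5 of the zone's 20 percentage points. On the maximum-HR base it is always larger, and in 22 of 30 assumed pairs without a beta-blocker, and all 27 usable pairs with one, it covers the whole zone. The 25% follows from the article's percentages alone. The bpm values and grid counts rest on assumed ages and resting rates.

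The consequence is an unclear safety rule and an attainment result whose upper reference is uncertain. The primary analysis, the between-group comparison of change in comfortable walking speed, does not use HR and is untouched. This is an inconsistency to correct, not a threat to the main result.

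**What to change.** Reconcile Standard Precautions with the two training-paradigm sections, the HR-zone section and Table 2. State the base of the 75% and which limit staff actually applied. This review proposes no limit and takes no view on which is right.

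Judge target-HR attainment against the limit applied, by arm, using the minute-by-minute HR. One suitable table gives the share of minutes below 60%, 60–75%, 75–80% and above 80% of reserve. The resting HR taken before each session and the stated formulas allow these bands to be computed. Report intensity reductions and individually modified limits only if they were logged, since the article does not say that they were.

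Data collection ended in January 2016, so this is a reporting correction. It costs a change of wording and one extra table, and the attainment figure may become less favourable.

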### Assessments

We used various functional mobility assessments at different time points - pretraining (baseline), midterm, posttraining (final), and 6-month follow-up, conducted by the physical therapist on our study at the LocoLAB. We used the 10-meter walk test to measure participants’ CWS and fast walking speed (FWS) [47], and the 6-min walk test (6MWT) [48] to measure walking capacity using an 85-feet oval walkway. At baseline, participant’s hemiparetic severity and ambulation category were classified using the lower extremity Fugl-Meyer, and functional ambulation category scale [49], respectively. We also used the Mini-Mental Scare Examination as a screening tool for participants’ cognitive function (>24) [50]. We also used the Berg-Balance Scale (BBS) [51] and Dynamic Gait Index [52] to measure participants’ balance function. We used the Activities-specific Balance Confidence (ABC) scale [53] to evaluate participants perceived balance function during activities of daily living, and the Geriatric Depression Scale (GDS) [54] and Stroke Impact Scale (SIS) [55] to assess participant’s mental function and perceived impact of poststroke disability on their quality of life, respectively. Participants were assessed at baseline, midterm, final (after 6 weeks), and at 6-month follow-up. Table 3 describes the assessments performed during these periods.

**Table 3 table3:** Timeline for assessments and collection of outcome variables at various study stages.

Baseline		Midterm	Final	6-month follow-up
Comfortable walk speed (CWS)		CWS	CWS	CWS
**Fast walk speed (FWS) using**		FWS	FWS	FWS
	10-meter walk test (10MWT)	6MWT	6MWT	6MWT
	6-min walk test (6MWT)	BBS	BBS	BBS
Fugl-Meyer lower extremity score		GDS	GDS	GDS
Functional Ambulation Category		—	DGI	DGI
Berg Balance Scale (BBS)		—	ABC	ABC
Dynamic Gait Index (DGI)		—	SIS	SIS
Geriatric Depression Scale (GDS)		—	—	—
Stroke Impact Scale (SIS)		—	—	—
Activities-Specific Balance Confidence (ABC)		—	—	—
Mini-Mental State Examination (MMS)		—	—	—

